#### Participant timeline

There are 15 regional referral hospitals each with a catchment of ~25 cART sites. Each team of three research assistants requires 4 weeks to enrol HCPs in one regional catchment. Follow-up at each cART site begins after its enrolment and lasts 30 months. The 30-month follow-up period is considered adequate to monitor durability of the real-life impact of the app on ADR reporting. Four additional months will be required to wrap-up the study, thus, 36 months overall (table 1).

**Table 1 T1:** Schedule of enrolment, interventions and assessments

	Study period						
	Baseline	Follow-up schedule					Close-out
Procedures	(t_0_)	t_0_+3 months	t_0_+6 months	t_0_+12 months	t_0_+15 months	t_0_+30 months	t_0_+36 months
**Enrolment**							
Eligibility screen	×						
Informed consent	×						
Allocation to study arm	×						
**Interventions**							
Mobile app arm	x	x	x	x	x	x	
Comparison arm	x	x	x	x	x	x	
**Assessments**							
Quantitative survey	x			x			
Mobile app data	x	x	x	x	x	x	
Economic cost data	x	x	x	x			
Interim data analysis					x		
Qualitative study	x			x			
Endline data analysis							x

#### Sample size

To estimate the number of cART sites required per arm for an effect size of 25%,^26^ we assume power of 80% at the 95% confidence level, mean of 1.0 IPT-linked ADR/month/100 000 treated PLHIV (0.00001) and SD of 1.179 IPT-linked ADRs/month/100 000 treated PLHIV (0.00001179) (SD was computed based on the monthly IPT-linked ADR reports submitted to NPC for 1 year from October 2018 to September 2019), cluster size of 10 HCPs and coefficient of variation of 0.25,^26^ which yields ~114 cART sites per trial arm or 228 in both study arms. A minimum of 189 cART sites per arm or 378 in both study arms (66% increment) will be required to cater for the following limitations: (1) the large proportion of HCPs who do not own smartphones of ~50%–60% as previously estimated^21 22^ – and is 26% (95% CI of 23% to 30%) from limited rollout of RCT; (2) refusal to participate by eligible HCPs of ~5% as previously estimated^27^ – and is 0% (95% CI of 0% to 2%) from limited rollout of RCT; (3) loss to follow-up due to the relatively long follow-up period of 30 months (~10%); and (4) contamination due to information sharing between study arms through social media (~30%).^28^ We shall enrol 382 cART sites (191 per study arm) to cater for other unforeseen limitations; thus, recruiting up to 3820 HCPs (1910 HCPs per trial arm). Limited rollout of the RCT suggests a cluster size of 7.2 (629/87) HCPs. We shall retain the average cluster size of 10 HCPs because the RCT has not yet enrolled from the central region of Uganda (with the country’s capital city) where cART sites tend to be much larger with more HCPs per site than the more rural eastern, western and northern regions.

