Although DTG is generally well tolerated, it is associated with serious ADRs including hyperglycaemia,^10–13^ neuropsychiatric effects (1.7%)^14^ and hepatotoxicity (0.1%).^15^ DTG is also associated with more common, but less serious, ADRs such as headache, abnormal dreams and abdominal pain, but the impact of these has not been evaluated in real-world settings in developing countries. The rapid rollout of DTG and scale up of IPT will increase the number of PLHIV exposed to these therapies, potentially increasing the incidence of ADRs, including serious ADRs, associated with these medicines. Discontinuation of DTG and/or IPT is recommended if serious ADRs such as jaundice, blurred vision or hyperglycaemia occur.^16^ Four in 100 000 PLHIV who receive IPT die due to an IPT-related adverse event.^1^

ADRs can reduce quality of life for PLHIV and increase morbidity, mortality and healthcare costs.^17 18^ In 2016, prior to DTG rollout, the NPC attempted to improve spontaneous ADR reporting via a web form. However, they received only 92 online reports versus 290 paper-based ADR reports linked to cART from October 2018 to September 2019. More recently, a PV task force composed of the NPC, the AIDS Control Program and Ministry of Health was set up. The task force established an active drug safety monitoring and management programme to complement the spontaneous ADR reporting system. The NPC received 109 DTG-linked ADR reports from October 2018 to September 2019 from ~348 000 PLHIV. Only 18 IPT-linked ADR reports were received from January 2019 to June 2019 from ~300 000 PLHIV: 2.6 DTG-linked ADR reports per month per 100 000 treated PLHIV and 1.0 IPT-linked ADR report per month per 100 000 treated PLHIV. These rates are barely 5% the known incidence of the ADRs in PLHIV elsewhere.^1 3^

The Med Safety mobile application was developed by the European Union Innovative Medicines Initiative: WEB-Recognising Adverse Drug Reactions. The same technology that produced the Med Safety App was also adopted by European countries including UK’s Medicines and Healthcare products Regulatory Agency (MHRA) in July 2015, Netherlands’ Lareb in January 2016 and Croatia’s HALMED in May 2016. In 2017, the Med Safety App was introduced in Africa (Burkina Faso and Zambia) in partnership with WHO. MHRA adapted Med Safety for low-income and middle-income countries (LMICs) including Uganda with approval from Uganda’s National Drug Authority (NDA) (figure 1).^4^
^,^

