## Methods and analysis

### Participants, interventions and outcomes

#### Study setting

The study will be conducted nationwide at 382 (of 1832 cART sites) high volume accredited cART sites in Uganda. The 382 cART sites serve 80% of the PLHIV on cART in Uganda.^8^ This protocol follows the Standard Protocol Items: Recommendations for Interventional Trials 2013 statement (online supplemental file 1).^23^

10.1136/bmjopen-2022-061725.supp1Supplementary data

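### The stated 80% power for a 25% increase does not follow from its inputs: the SD is the monthly variation of a national series, and the coefficient of variation gives 114 sites only if entered as an ICC

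*Protocol article*

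**What the plan says.** All references are to the protocol article. Its Sample size section sets the target ("To estimate the number of cART sites required per arm for an effect size of 25" per cent) and the error rates ("we assume power of 80% at the 95% confidence level"). The planning rate is a "mean of 1.0 IPT-linked ADR/month" per 100,000 treated PLHIV, with an SD of 1.179 on the same scale. On the source of that SD it states: "SD was computed based on the monthly IPT-linked ADR reports submitted to NPC for 1 year from October 2018 to September 2019". The clustering inputs are "cluster size of 10 HCPs and coefficient of variation of 0.25", "which yields ~114 cART sites per trial arm or 228 in both study arms". The 114 is then raised by 66% to 189 for smartphone non-ownership, refusal, loss to follow-up and contamination, and rounded up to 191 per arm.

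The Effectiveness section repeats the 25% effect and 80% power. It compares arms at cluster level by t-test or Wilcoxon test. Under Outcomes, the primary outcome is a count of HCP-reported ADRs over person-months of treated PLHIV. Under Unit of analysis, the unit is the site.

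**The concern.** A comparison of site rates needs the variance of a site's 30-month rate. That variance has two parts: the chance variation of a small count, and true differences between sites. Twelve monthly totals from one national system measure neither. They also give no SD for an individual HCP, and a site's information comes from its PLHIV person-months and its number of reports, not from how many HCPs work there.

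Two smaller faults come with this. The parameter called a coefficient of variation appears to have been used as an ICC. And the mean matches January to June 2019, while the SD covers October 2018 to September 2019.

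At stake is how a null result is read. With 80% power for 25% on record, a non-significant comparison would be taken as fair evidence that the app does not raise reporting. If the real power is much lower, that reading is unsafe.

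**Working it through.** **1. Reproducing 114.** Inputs from Sample size: mean 1.0, difference 0.25, SD 1.179, 10 HCPs per site, 0.25 for clustering, 80% power. A two-sided 5% test is assumed, as sidedness is not stated.

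- Individuals per arm: 2 × (1.96 + 0.8416)² × 1.179² / 0.25² = 349.1.
- Design effect with 0.25 as an ICC: 1 + 9 × 0.25 = 3.25.
- Sites per arm: 349.1 × 3.25 / 10 = 113.5, so 114. This matches. (A one-sided test would give about 90.)

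**2. The same inputs with 0.25 as a between-cluster CV.** The standard formula gives 1 + 7.849 × [(2 × 1.179²)/10 + 0.25² × (1² + 1.25²)] / 0.25² = 56.03, so 57 per arm. The label and the result disagree, in the direction of too many sites.

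**3. What the SD would have to be.** The plan's calculation implies an SD of the site rate of 1.179 × √(3.25/10) = 0.67 on a mean of 1.0. For 80% power with 191 sites per arm it may be at most 0.25/2.8016 × √(191/2) = 0.87.

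**4. Expected counts at the documented rates.** The Introduction reports "Only 18 IPT-linked ADR reports were received from January 2019 to June 2019" from about 300,000 PLHIV: 18/6/300,000 = 1.0 per 100,000 per month. It gives 2.6 for DTG, from about 348,000. Study setting says: "The 382 cART sites serve 80% of the PLHIV on cART in Uganda". Follow-up is 30 months. Assumption: the 80% share applies to both drugs and exposure stays constant.

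- IPT: 300,000 × 0.8 / 382 = 628 PLHIV per site; × 30 × 0.00001 = 0.188 reports per control site; × 191 = 36 in the arm.
- DTG: 348,000 × 0.8 / 382 = 729 per site; × 30 × 0.000026 = 0.568 per site; × 191 = 108.6 in the arm.
- Combined: 0.757 per site, 144.6 in the arm.

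Chance variation alone then gives a site-rate SD, relative to the mean, of 1/√0.188 = 2.3 for IPT and 1/√0.757 = 1.15 combined. Both exceed 0.87.

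**5. Power for a rate ratio of 1.25, 191 sites per arm.** Var(log RR) = 1/E₀ + 1/(1.25 E₀) + 2 CV²/191, where E₀ is the control-arm count; power = Φ(0.2231/√Var − 1.96).

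| Control-arm reports | CV 0 | CV 0.25 | CV 1 |
|---|---|---|---|
| 36 (IPT only) | 17% | 17% | 15% |
| 144.6 (DTG + IPT) | 52% | 50% | 31% |
| 289.2 (combined, doubled) | 81% | 77% | 41% |

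Worked cell (DTG + IPT, CV 0.25): Var = 1.8/144.6 + 0.125/191 = 0.01310; 0.2231/0.1145 = 1.949; Φ(−0.011) = 50%.

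Simulation of the planned tests agrees approximately. At 0.757 reports per site and CV 0.25, the t-test has 52% and the Wilcoxon test 46%; at CV 1, 31% and 27%.

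**6. What 80% would take.** Var must be (0.2231/2.8016)² = 0.00634. At CV 0.25 this needs 1.8/(0.00634 − 0.00065) = 316 control-arm reports. Above a CV of √(0.00634 × 191/2) = 0.78, no number of reports is enough with 191 sites per arm. At CV 0.25 the rate ratio detectable with 80% power is 1.80 for IPT only and 1.37 combined.

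All these figures precede the roughly 10% loss and 30% contamination that the article itself expects.

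**The case against.** The strongest reply is that power is unknown rather than shown to be low. The article gives no site-level variance, so the range of CVs above is an assumption. Exposure is unlikely to stay at 2019 levels: the Introduction describes rapid DTG rollout and IPT scale-up, and both arms receive training and reminders. Doubling the combined count restores 77–81% if the CV is at most 0.25.

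The outcome could also be read more broadly. The Introduction counts 92 online and 290 paper reports linked to cART in one year. On the same scaling, 382 × 2.5 years × 0.8 / 2 = 382 control-arm reports, which gives 86% power at CV 0.25 and 44% at CV 1. That is an upper reading, because these reports include other regimens and the aims concern DTG and IPT.

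This stands, and it rules out a tempting stronger reading: that 191 sites per arm cannot have 80% power. The documents do not show that.

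A second tempting reading is that confusing a CV with an ICC cost power. It did not; taken alone it doubles the number of sites. A reader might also notice that 57 per arm is 114 in both arms and infer that a total was mistaken for a per-arm figure. The article does not say how 114 was obtained, and the ICC route also gives 114 as a per-arm figure, so that inference is not supported.

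None of this supplies the missing step. No between-site SD or ICC is stated, and the claimed 80% still does not follow from the inputs given.

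**Conclusion.** The point holds as a failure of derivation. The 80% power in Sample size and Effectiveness rests on an SD that measures the wrong variation, and on a parameter whose label does not match the use that reproduces the result. The CV/ICC discrepancy is conservative in itself, so any shortfall comes from the SD.

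The low-power figures, about 15–17% for IPT alone and 31–52% for DTG plus IPT, are conditional on 2019 exposure and reporting rates, an 80% share of PLHIV at the 382 sites, constant exposure over 30 months and a between-site CV of 0 to 1. Growth in exposure or reporting could bring power close to 80% where sites differ little, but not where they differ widely. The stated power should be corrected before it is relied on to interpret a null result.

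**What to change.** Keep the 382 sites. Recompute the power for a 25% increase, or the detectable rate ratio, for 191 sites per arm. Base it on site-level report counts and PLHIV person-months for the combined DTG/IPT outcome, and match it to the planned cluster-level comparison. Take the control rate and between-site CV from NPC data by site where these exist, or from arm-blinded pooled counts at the 87 rollout sites. If neither is available, show power over a stated range of rates and CVs. Carry the expected loss and contamination through the calculation.

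Restate the power in both Sample size and Effectiveness. Say whether 0.25 is an ICC or a CV, and correct the 114 accordingly. Take the mean and any variance from the same period.

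The cost is a recalculation and revised wording, with no extra sites. The downside is that the stated power may become less favourable.

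### The 66% inflation to 189 sites per arm leaves the 25% effect untouched, so on the protocol's own base it does not cover the 30% contamination it lists

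*Protocol article*

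**What the plan says.** All the figures are in the Sample size section of the protocol article.

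- **Base.** The plan gives about 114 sites per arm for a 25% effect: "we assume power of 80% at the 95% confidence level", a mean of 1.0 and an SD of 1.179 IPT-linked reports per month per 100 000 treated PLHIV, "cluster size of 10 HCPs", and a 0.25 labelled a coefficient of variation.
- **Increment.** "A minimum of 189 cART sites per arm or 378 in both study arms (66% increment) will be required". Enrolment is then set at 191 per arm for unforeseen limitations.
- **What the increment covers.** Four items: smartphone non-ownership (previously put at 50–60%, 26% in the limited rollout); refusal (previously 5%, 0% in the rollout); "loss to follow-up due to the relatively long follow-up period of 30 months (~10" per cent); and "contamination due to information sharing between study arms through social media (~30" per cent).

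The section does not say how the 66% was formed, and it does not lower the 25% effect for any of the four items.

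Other sections fix how the data are analysed. Outcomes counts HCP-reported ADRs over treated PLHIV by arm. Quantitative data takes all reports received from the sites, by intention to treat and per protocol. Effectiveness compares arms at cluster level and repeats the 25% effect and 80% power.

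**The concern.** Loss and contamination act differently on a sample size. A lost site leaves the analysis, and dividing by the retained fraction restores the number. A contaminated comparison site stays in an intention-to-treat analysis and pulls the two arms together, so the required number grows with the inverse square of the remaining difference. An increment that leaves the effect at 25% does not provide for this.

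At stake is the claim that 189 sites per arm are enough once these limitations are allowed for. If power is below 80% under the contamination the sponsor itself expects, a null result could be read as evidence that the app does not work when the trial could not reliably show the effect.

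**Working it through.** **Inputs** (Sample size section): difference 0.25 (1.00 to 1.25), SD 1.179, 10 HCPs per site, clustering parameter 0.25, power 80%, loss 10%, contamination 30%. Sidedness is not stated; two-sided 5% is assumed, so the multiplier is (1.960 + 0.842)² = 7.849.

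**1. Reproduce 114.**
- Individuals per arm = 2 × 1.179² × 7.849 / 0.25² = 349.1.
- Design effect with 0.25 as an intracluster correlation = 1 + 9 × 0.25 = 3.25.
- Sites per arm = 349.1 × 3.25 / 10 = 113.5, i.e. 114.

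**2. Reproduce 189.**
- 26 + 0 + 10 + 30 = 66, and 114 × 1.66 = 189.2. This uses all four listed values and matches both printed figures.
- It is not the only route to 189: 113.47 / (1 − 0.40) = 189.1 (loss plus contamination only), and 113.47 / (0.95 × 0.90 × 0.70) = 189.6 (5% refusal, no smartphone term). Both of these also treat contamination as lost units.
- If all four items were pure losses, compounding them would need 113.5 / (0.74 × 0.90 × 0.70) = 243 per arm (245 from the rounded 114), above 191.

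**3. Contamination as dilution.** Assume 30% of the effect carries over to the comparison arm.
- Difference = 0.25 × 0.70 = 0.175.
- Sites per arm = 113.5 / 0.70² = 232; with 10% loss, 232 / 0.90 = 257.

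**4. Power at the planned size.** Sites left after 10% loss = 191 × 0.90 = 172.
- Standard error = √(2 × 1.179² × 0.325 / n) = 0.0688 at 191 and 0.0725 at 172.
- Power at 191 = Φ(0.175 / 0.0688 − 1.96) = 72%.
- Power at 172 = Φ(0.175 / 0.0725 − 1.96) = 68%.

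| Dilution (172 per arm) | Difference | Power |
|---|---|---|
| 0% | 0.2500 | 93% |
| 15% | 0.2125 | 83% |
| 20% | 0.2000 | 79% |
| 30% | 0.1750 | 68% |

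- Largest dilution that keeps 80% power: 1 − √(113.5/172) = 19%, or 1 − √(113.5/191) = 23% without loss.
- Detectable difference at 172 = 2.802 × 0.0725 = 0.203, about 20% between arms, or 0.203 / 0.70 = 29% before contamination.

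**5. If 0.25 is a true coefficient of variation.**
- The Hayes–Bennett formula gives 1 + 7.849 × [2 × 1.179²/10 + 0.25² × (1.00² + 1.25²)] / 0.25² = 56.0, taken as 57 per arm.
- With contamination (means 1.075 and 1.25) it gives 116 per arm, or 129 with loss, which 191 covers. Power at 172 is about 93–94%; the two ends differ only in which arm means enter the variance term.

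**6. Non-ownership under its two readings** (0.25 as an intracluster correlation).
- Owners only count: cluster size 10 × 0.74 = 7.4, so sites = 349.1 × (1 + 6.4 × 0.25) / 7.4 = 123 per arm. With contamination as dilution, 123 / 0.49 is about 250.
- All HCPs' reports count, and the 25% refers to those able to use the app: difference = 0.25 × 0.70 × 0.74 = 0.1295, and power at 172 = Φ(0.1295 / 0.0725 − 1.96) = 43%.

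**The case against.** Four points can be made for the plan.

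- **The route to 66% is not stated.** A reader might infer from 26 + 0 + 10 + 30 that percentages were simply added. The match is exact, but other routes also give 189, so addition cannot be asserted as what was done. This stands. It does not rescue the figure, because every route found treats contamination as lost units.
- **The shortfall depends on what 0.25 is.** The text calls it a coefficient of variation. Taken literally, 191 sites per arm cover contamination plus loss with room to spare. This stands as a condition on the verdict. But 114 is the base the protocol prints and inflates, and it reproduces per arm only with 0.25 as an intracluster correlation.
- **30% contamination need not mean 30% of the effect is lost.** Its meaning rests on a cited source not available here. If 30% of comparison HCPs hear of the app and fewer use it, dilution is smaller, and at 15% power is still 83%. Dissemination strategies also plans arm-specific communication to limit contamination, and Compliance with allocation plans coding to assess cross-over. This is why power belongs over a range. The planned per-protocol analysis does not protect the intention-to-treat comparison.
- **Non-ownership may not dilute anything.** A reader might go further and put power at 43% by discounting for non-owners as well. The documents do not establish this. Eligibility criteria admits only smartphone owners, and the rollout cluster size of 7.2 is close to 7.4, so non-ownership may only shrink the cluster. Aims and objectives can also be read as stating the 25% at site level, already including incomplete app use. On the other side, Intervention arm introduces the app to owners and non-owners alike, and all site reports are analysed. The sections need reconciling first.

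**Conclusion.** The statement that 189 sites per arm cater for the listed limitations is not supported on the protocol's own base, because contamination is never taken out of the 25% effect. The need is about 232 sites per arm, or 257 with 10% loss, against 191 enrolled, and stated power of 80% becomes about 72% or 68%. This rests on three assumptions: two-sided 5% testing, 0.25 acting as an intracluster correlation, and 30% of the effect carrying over to comparison sites. It does not depend on how non-owners are treated.

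A flat statement that the trial is underpowered would go too far. With a true coefficient of variation of 0.25, or dilution below about 19%, the planned number holds 80% power after loss. The 43% figure is conditional on non-owners' reports counting and on the 25% applying only to HCPs able to use the app.

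**What to change.** Keep 191 sites per arm and rewrite the inflation step.

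1. State how the inflation is formed. Divide by (1 − loss) for true losses, and put contamination into the effect size, so that sites = base / [(1 − contamination)² × (1 − loss)].
2. Replace the claim that 189 sites cater for the limitations with power over a range of contamination (on the current base with 172 sites: 83%, 79% and 68% at 15%, 20% and 30%), or with the detectable effect (about 20% between arms, about 29% before contamination).
3. State whether 0.25 is an intracluster correlation or a true coefficient of variation, and give the base that follows (about 114 or about 57 per arm).
4. Reconcile Eligibility criteria with Intervention arm on whether reports from non-owners count and whom the 25% describes. Only then treat non-ownership as dilution or as a smaller cluster.

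The cost is a recalculation and, if 0.25 is an intracluster correlation, a less favourable stated power. No sites are added and the analysis is unchanged.

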### Assignment of interventions

#### Unit of randomisation

This unit is a cluster, defined as an cART site located at each of the 382 prescreened health facilities and consisting of HCPs and DTG/IPT-treated PLHIV. The use of cART sites as clusters minimises cointervention, duplication of reporting and organisational challenges and provides valid PLHIV population denominators for analysis of the outcomes.

#### Concealment of sequence generation

Using the sealed envelope software, an independent Biostatistician from the Clinical Epidemiology Unit at Makerere University, who will not participate in the subsequent data analyses, generated the simple randomisation sequence.

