**Methods and analysis:**

A pragmatic cluster-randomised controlled trial will be implemented over 30 months at 191 intervention and 191 comparison cART sites to evaluate Med Safety. Using a randomisation sequence generated by the sealed envelope software, we shall randomly assign the 382 prescreened cART sites to the intervention and comparison arms. Each cART site is a cluster that consists of healthcare professionals and PLHIV receiving dolutegravir-based cART and/or isoniazid preventive therapy. Healthcare professionals enrolled in the intervention arm will be trained in the use of mobile-based, paper-based and web-based reporting, while those in the comparison arm will be trained in paper-based and web-based reporting only.

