#### Randomisation

The prescreened cART sites will be assigned by research assistants to the intervention and comparison arms, figure 2, using an electronically generated simple randomisation sequence.

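### The stated 191 sites per arm and 189 minimum do not follow from simple randomisation of 382 sites; the power cost is negligible, but the text needs reconciling and the primary comparison should always adjust for region and site size

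*Protocol article*

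**What the plan says.** Arm sizes. The Abstract plans the trial at "191 intervention and 191 comparison cART sites". The Sample size section repeats this ("We shall enrol 382 cART sites (191 per study arm") and sets a floor: "A minimum of 189 cART sites per arm or 378 in both study arms (66% increment) will be required". The floor already contains the allowance for loss to follow-up, so it is a number to be randomised.

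Method. Concealment of sequence generation says that the independent biostatistician "generated the simple randomisation sequence". The Randomisation section says that sites are assigned "using an electronically generated simple randomisation sequence". Neither section mentions blocks, strata, matching or a constraint on totals. The list was known beforehand: under Unit of randomisation, clusters are "located at each of the 382 prescreened health facilities".

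Site differences. The Sample size section describes the central region as one "where cART sites tend to be much larger with more HCPs per site than the more rural eastern, western and northern regions". Participant timeline describes 15 catchments of about 25 sites, each taking a team four weeks to enrol.

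Analysis. Effectiveness specifies a t-test or Wilcoxon rank-sum test at cluster level. Success of randomisation compares the arms on location, facility level, number of PLHIV and other features. Multivariable analysis brings in covariates only if that comparison suggests that randomisation did not work.

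**The concern.** Simple randomisation is in effect an independent coin toss for each site. It fixes no totals, so a plan that promises 191:191 and requires 189 per arm describes something its method delivers only by luck. Either simple is the wrong word for what was done, or the arm counts are expectations presented as facts. A reader of the final report could not tell an ordinary split such as 183:199 from a departure from protocol.

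The second part concerns balance. All 382 sites were known in advance, and the article itself points to a regional difference in site size, yet nothing in the allocation balances region or size. Control of these features is left to the analysis, where it depends on the result of a baseline check. That is a weak trigger. With proper randomisation, baseline differences arise by chance, so testing them does not show whether randomisation worked. Choosing the analysis after seeing them also leaves the primary result less firmly fixed in advance.

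**Working it through.** **1. The plan's own figures (Sample size).** Inputs: difference 0.25 (25% of a mean of 1.0), SD 1.179, 80% power, two-sided 5% (assumed from the 95% confidence level), cluster size 10, and 0.25 entered for clustering.
- Individuals per arm: 2 × (1.960 + 0.842)² × 1.179² / 0.25² ≈ 349.1, rounded up to 350.
- Design effect: 1 + (10 − 1) × 0.25 = 3.25.
- Sites per arm: 350 × 3.25 / 10 = 113.75, so 114.
- After the 66% increment: 114 × 1.66 = 189.2, so 189.

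The stated 114 and 189 reproduce. (They do so only with 0.25 used as an intracluster correlation, although the article labels it a coefficient of variation. That is a separate matter.)

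**2. What simple randomisation gives.** Let X be the number of sites in one arm, X ~ Binomial(382, 0.5), with SD √382 / 2 = 9.8.
- P(X = 191) = 0.041.
- Both arms reach 189 only if 189 ≤ X ≤ 193: P = 0.202. The stated minimum is missed with probability 0.798.
- The 2.5% and 97.5% quantiles are 172 and 210.
- P(both arms at least 114) exceeds 0.9999.

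**3. What that costs in power.** For arms of a and b sites, the equivalent equal-arm size is the harmonic mean, 2ab / (a + b).

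| Split | Effective sites per arm | Power, if 189 per arm gives 80% |
|---|---|---|
| 191:191 | 191.0 | 80.4% |
| 181:201 | 190.5 | 80.3% |
| 172:210 | 2 × 172 × 210 / 382 = 189.1 | 80.0% |

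At 171:211 the effective size is 2 × 171 × 211 / 382 = 188.9. The effective size therefore stays at or above 189 exactly when the split is no worse than 172:210. P(|X − 191| ≥ 20) = 0.046, so an effective 189 is met with probability 1 − 0.046 = 0.954.

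**4. Balance of region and size.**
- One catchment of 25 sites: P(17:8 or worse, either direction) = 0.108. At least one such split among 15 catchments: 1 − (1 − 0.108)^15 ≈ 0.82. These splits can favour either arm and partly cancel.
- Share of treated PLHIV in one arm: SD ≈ 0.5 × √((1 + CV²) / 382), where CV is the coefficient of variation of treated PLHIV per site. The article gives no CV, so a range is assumed. CV 0.5: SD 0.029, 95% range 44% to 56%. CV 1.0: SD 0.036, 43% to 57%. CV 1.5: SD 0.046, 41% to 59%.

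**The case against.** The strongest reply is that almost nothing is lost. A reader might infer from the 20% figure that the trial will probably be too small. The article does not support that: power follows the harmonic mean, an effective 189 is met about 95% of the time, and the 189 already stands 66% above the calculated 114. This part of the reply stands in full.

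A reader might also infer that the method leaves the arms biased or unbalanced. That does not follow either. Simple randomisation balances in expectation, chance imbalance is covered by the test's type I error, and 382 clusters limit its overall size. Nor does the article show that sites differ greatly in patient numbers. Its remark about the central region is tied to HCPs per site, all 382 sites were chosen as high-volume, and no distribution of PLHIV is given. The outcome is a rate per treated PLHIV compared at site level, so a large site counts as one observation. What remains is that region and size are not balanced by design, which is a matter of precision and credibility rather than validity.

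Third, the sequence is described as already generated. The figure of 191 may be the realised split, or simple may have been used to mean unstratified. The flow diagram is not shown, so the text cannot settle it. This limits the first part to a conflict of wording, but does not remove it.

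Finally, one might propose re-randomising the sites not yet opened, since the limited rollout covers 87. The gain cannot be estimated from the article, and replacing a concealed list in mid-trial creates two allocation phases and invites questions about its integrity. That step is not justified.

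**Conclusion.** The point holds as a correction to the text and a modest improvement to the analysis. The stated arm sizes are not a property of the stated method: 191:191 has probability 4%, and at least 189 in both arms 20%, assuming independent 1:1 allocation of all 382 sites with no undisclosed restriction. The cost in power is about 0.4 percentage points at the edge of the 95% range, which is negligible. There is no bias.

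Region and site size are left uncontrolled at allocation, and the analysis takes them up only conditionally. How much precision this forgoes cannot be computed, because the article gives neither the spread of PLHIV per site nor the association of region or size with reporting. The case for unconditional adjustment rests on the article's own remark about central-region sites and on fixing the primary analysis in advance.

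**What to change.** Keep the existing sequence and make three changes.

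1. Reconcile the Abstract and Sample size with Concealment of sequence generation and Randomisation. If totals were forced to 191:191, name the restriction and drop the word simple. If not, replace 191 per arm with the counts that the sequence produced.
2. State the 189 requirement as an effective number per arm, 2ab / (a + b), which any split from 172:210 to 210:172 satisfies.
3. Specify that the primary cluster-level comparison adjusts for region (or catchment) and baseline number of treated PLHIV, whatever the baseline comparison shows. A regression of the site rate on arm, region and PLHIV number would replace the t-test; a rank test stratified by region and size group would replace the Wilcoxon test. Adjusting for catchment would also absorb differences in start date between catchments. The unadjusted comparison can stay as a supporting analysis.

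The cost is some extra analysis work and, with four regions and one size term, 3 + 1 = 4 degrees of freedom out of 382 − 2 = 380 (14 + 1 = 15 with catchments). Both adjustment variables are already on the list for the baseline comparison. The change should be recorded before the interim analysis. Because the analysing biostatistician is to be blinded, unequal counts should carry neutral arm labels until the code is broken.
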